### Recruitment {15}

In the health areas where the study is taking place, study staff will be deployed to pre-screen children in the villages. The pre-screeners will move door to door and seek to identify children that are in the age range of 6–59 months with a MUAC >125 mm but WAZ <−3. Pre-screeners will be equipped with a calendar that helps the estimation of age as well as an electronic weight scale and tablet that calculates the exact WAZ score of the child. Once a child has been screened eligible by the pre-screener, they will receive a screening card and instructions to visit the IRC research team at the closest health center on a given day when research activities are taking place. Eligibility will be confirmed at the research site prior to proceeding to consent and participation.

## Assignment of interventions: allocation

### Sequence generation {16a}

The random sequences will be generated in STATA by one of the data managers. Stratified, blocked randomization will be used. Stratification will be done by recruitment site, i.e., separate random sequences will be generated for each of the eleven sites. Blocked randomization will be used, with varying block sizes.

### Concealment mechanism {16b}

Treatment allocation will be blinded to the investigators until data cleaning and initial data analyses have been completed. The main data file will contain an intervention code, which will need to be unblinded to know which code corresponds to which group. The intervention code will be kept in a separate file, only available to the person responsible for the provision of randomization lists. Once data collection and data cleaning are complete, the intervention code will be released to the investigators.

### Implementation {16c}

The random sequences will be generated by one of the data managers. Enrolment will be done by study staff present at the research sites. Participants will be given consecutive health center-specific study ID numbers that will determine to which study arm they belong to, according to the random sequences. The person giving the study ID will not have access to the randomization list. Thus, the randomization arm of the newly enrolled child will only be revealed to the study team and to the caregiver when the child has been enrolled.

## Assignment of interventions: blinding

### Who will be blinded {17a}

This is an open trial since participants cannot be blinded with respect to the intervention they are receiving. Study staff will also not be blinded. However, treatment allocation will be blinded to the investigators until data cleaning and initial data analyses have been completed.

## Data collection and management

### Plans for assessment and collection of outcomes {18a}

#### Socio-economic questions

A socio-economic questionnaire will be administered upon enrolment to the study. Information will be collected through an individual interview with the caregiver. The questions include socio-economic indicators, family size, and main income sources of the household.

#### Anthropometry

Weight, height, MUAC, and edema will be measured in all children at every visit. All measures will be performed and recorded twice by alternating the roles of the measurer and the assistant, and the mean used for analysis. Weight will be measured to the nearest 0.1 kg with an electronic scale (SECA scale). Length and height will be measured to the nearest 0.1 cm with a wooden height board with graduated index strips in millimeters (UNICEF model). MUAC will be measured with a non-stretchable white MUAC tape on the left arm to the nearest millimeter (mm).

#### Body composition

Body composition will be measured both by measuring skinfold thickness as well as the bioelectrical impedance. Body composition will be measured at enrolment and at 8 and 24 weeks from enrolment.

Skinfold thickness will be measured with the GIMA code 27346 device that gives an electronic reading of the result with 1mm precision. Skinfold thickness measures will be performed at the sub-scapular and triceps levels from the right side of the child with the child in a sitting position. Repeated measures will be performed for each site altering the measurer and the assistant. Bioelectrical impedance will be analyzed with the BodyStat 500 device that provides measurements for the resistance, reactance, and phase angle. A repeat measurement will be performed.

#### Hemoglobin

Hemoglobin will be measured at enrolment and at 8 and 24 weeks from enrolment using a HemoCue 301 device and by applying a finger prick technique to obtain a drop of peripheral blood. Devices will be checked regularly against Eurotrol control solutions for low and normal levels.

#### Clinical exam

The study nurses will conduct a standard clinical consultation at each visit for all children irrespective of study arm. The clinical exam will include a history of recent illness and the clinical assessment of the child (i.e., temperature, respiratory rate, pulse rate, cough, ear, and nasal discharges) according to the national protocol for the management of SAM [49]. Past and present symptoms, vital signs, diagnosis, and treatments prescribed will be recorded. The clinical assessment will also serve to monitor the development of complications that need inpatient care. All serious adverse events or development of complications will be immediately reported to the study supervisor and the child referred to inpatient treatment if needed. Adverse events include morbidities. Serious adverse events include death, development of any grade of edema, development of a MUAC <125mm, and development of medical complications requiring inpatient care.

Complications are based on the national CMAM referral criteria [49].

#### Training

Study staff will be trained on all study procedures specific to their role during a 2-week-long theoretical and practical training. A standardization exercise as per the ENA SMART survey will be performed prior to the launch of the study to ensure the capacity of the polyvalent agents to accurately and precisely perform all anthropometric and body composition measurements. In case of non-conform results, re-training will be arranged and a new standardization organized until results return with acceptable accuracy and precision. Periodic anthropometric standardization exercises will be performed during the trial.

### Plans to promote participant retention and complete follow-up {18b}

In recognition of the efforts caregivers make when participating to the study, they will receive a small compensation of 1000 cfa at each visit aimed at offsetting the opportunity and travel cost of participation.

Participants will be encouraged to attend all study visits and reminders will be done through telephone and home visits by community focal points. Continuation of study visits until 6 months post-enrolment will be encouraged regardless of treatment outcomes (defaulting, non-response, etc.).

### Data management {19}

All questionnaire data and measurements will be recorded through digital data collection using tablets and the software CommCare (https://www.dimagi.com/commcare/). A unique barcode with participant ID will be assigned to each child and used to identify the child at each visit. Data collected on the tablets is transferred automatically to the data base on the server and aggregated to the existing patient record and data base. Data will be treated with the help of automated error identification within CommCare and through Power BI to check the coherence, consistency, and completeness. Regular supervision and refresher training workshops will be organized to maintain a high data quality.

Data will be reviewed weekly to monitor the data quality and confirm a good balance in the allocation of children in the 3 study arms. Baseline data monitoring will include reporting the baseline anthropometric characteristics of children by arm, their age and sex distribution, and some basic socioeconomic variables. Outcome data quality monitoring will include looking into anthropometric measurements and checking the normality of their distributions, precision in terms of an even use of decimals and mean differences between 2 subsequent measurements, and looking for any unusual increments or reductions between measurements from subsequent visits. The quality of the intervention will be monitored by checking the concordance between the amount of RUTF received as specified by the study arm and the child's anthropometric measures.

### Confidentiality {27}

Personal identifiers, including names of participants and their date of birth, will be collected on paper registries and on the electronic data forms. Paper registries will be kept with the study staff at all times and in locked boxes when not in use. Personal identifiers are kept in the electronic data base as long as the study is running, to be able to cross-validate participant identity. After data cleaning and verification, personal identifiers will be removed from the data files. Photos and videos of participants will not be taken without caregiver’s specific consent (Supplementary file 2).

### Plans for collection, laboratory evaluation and storage of biological specimens for genetic or molecular analysis in this trial/future use {33}

No biological specimens will be collected in this trial. Hemoglobin and malaria rapid tests will be conducted using the finger prick method and extracting a drop of blood from the participant directly to the single-use microcuvettes for analysis. The results of the tests will be noted down and the biological waste including the finger prick device and the microcuvette disposed of immediately.

## Statistical methods

### Statistical methods for primary and secondary outcomes {20a}

In reporting the trial outcomes, we will follow the CONSORT 2010 statement for reporting parallel group randomized trials [50]. This will include reporting participant flow through the trial as per the CONSORT guidance [50]. All statistical analysis will be done using STATA® software or similar. Baseline characteristics will be reported by the study arm. Linear mixed models will be fitted to analyze the primary outcome and all continuous outcomes while logistic mixed-effects models will be fitted for binary or categorical outcomes. Random effects will include participants, study sites, and study teams. Adjustment for block randomization will be applied by means of random effects. Adjustment for confounders such as age and sex and outcome at enrolment will be included. To investigate effect modification, two-way interactions between intervention group and age group, sex, and degree of undernutrition (WHZ, WAZ and HAZ categories) will be assessed.

Anthropometric outcomes at 2 and 6 months post enrolment will be analyzed by adjusting for the exact number of days from enrolment to the measurement date. In addition, the treatment outcomes will be described for the 2 treatment groups, and the study exit status for all 3 study groups using count and percentage.

### Interim analyses {21b}

A data safety monitoring board (DSMB), comprising of independent members with experience in nutrition epidemiology and humanitarian nutrition, will review the outcomes and adverse events at mid-point of the trial.

### Methods for additional analyses (e.g., subgroup analyses) {20b}

Sub-group analyses will include children with (1) concurrent wasting (WHZ <−2) and stunting (HAZ <−2) versus only wasted versus only stunted, (2) severe wasting (WHZ<−3) versus moderate wasting (WHZ ≥−3 and −2) and no wasting (WHZ >−2) and (3) severe stunting (HAZ <−3) versus moderate stunting (HAZ ≥−3 and −2) and no stunting (WHZ >−2), at enrolment to study.

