## Introduction

### Background and rationale {6a}

The field of nutrition divides undernutrition into two categories: micronutrient deficiencies and growth deficits. Micronutrient deficiencies arise when specific type 1 micronutrients, such as iron, are lacking in the diet [1]. These deficits give rise to a specific symptom, anemia in the case of iron, that is rather easy to identify [2] and treat via supplementation [3, 4]. Type 1 micronutrients include all vitamins as well as some minerals such as iodine, copper, and calcium [1]. Growth deficits occur when either type 2 micronutrients or macronutrients are lacking in the diet leading to slowed height and weight gain. Type 2 micronutrients include zinc, potassium, and magnesium [1].

Growth deficits are further divided into the overlapping subcategories of wasting, stunting, and underweight [5]. Being wasted is strictly defined as a weight-for-height *z*-score (WHZ) below −2, stunted as a height-for-age *z*-score (HAZ) below −2, and underweight as a weight-for-age *z*-score (WAZ) below −2 [6]. Both being stunted and wasted overlap heavily with the category of children who are underweight [5]. Up to 93% of underweight children are also stunted or wasted and 17% accumulate a degree of both deficits [5].

All growth deficits are associated with an increased risk of mortality compared to children with no growth deficits. Moderately (*z*-score between −2 and −3) stunted, underweight, and wasted children have a 2.3-, 2.6-, and 3.4-fold increased risk of mortality, respectively [7]. Severe (*z*-score below −3) stunting, underweight, and wasting are associated with 5.5, 11.6, and 9.4 increased risk of mortality, respectively [7]. Accumulating several deficits increases substantially the mortality risk: children with both stunting and wasting, either moderate or severe, have a 12.3-fold increase in their risk of mortality [8].

Currently, only severe wasting is intentionally addressed via therapeutic feeding [9–11]. Children are admitted to therapeutic feeding programs for severe acute malnutrition (SAM) if their WHZ is below −3, they have a mid-upper arm circumference (MUAC) below 115 mm or in the presence of edema [12]. MUAC is used to detect being wasted as it reflects muscle mass deficits [13, 14], predicts mortality [15], is quick and easy to measure, and thus is used in community screening campaigns to identify malnourished children [9].

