### Eligibility criteria {10}

The study population will be composed of children living in the catchment area of 11 health centers of the Nara district where the study will be taking place. Inclusion criteria include (a) age between 6 and 59 months, (b) MUAC ≥125 mm, (c) WAZ <−3, (d) living in the study catchment area, and (e) expects to be able to continue follow-up visits for next 6 months. Children will not be included in the trial if they have (a) nutritional edema, (b) known peanut or milk allergy, (c) severe illnesses requiring inpatient level treatment (according to CMAM guidelines), (d) medical condition affecting food intake (lip and palate cleft, handicap etc.), and (e) has already taken part in the study.

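### The no-stunting level of the stunting subgroup is defined by WHZ instead of HAZ, so the groups overlap and leave children out; the pre-screening MUAC wording also needs reconciling

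*Protocol article*

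**What the plan says.** **Stunting subgroup.** Protocol article, Methods for additional analyses {20b}, lists three subgroup analyses by status at enrolment:

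- (1) "concurrent wasting (WHZ <−2) and stunting (HAZ <−2) versus only wasted versus only stunted", so stunting is HAZ below −2.
- (2) severe, moderate and no wasting, the last given as "no wasting (WHZ >−2".
- (3) "severe stunting (HAZ <−3) versus moderate stunting (HAZ ≥−3 and −2) and no stunting (WHZ >−2", so the two stunted levels use HAZ and the reference level uses WHZ.

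Background and rationale {6a} has "stunted as a height-for-age" z-score below −2. Statistical methods {20a} plans interactions of intervention group with HAZ, WHZ and WAZ categories but gives no cut-offs, so {20b} is the only place in the article where the analysis categories are spelled out.

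Under Intervention description {11a} and Table 1, standard-arm children with WHZ ≥−2 receive no RUTF, while every child in the simplified arm receives one sachet a day.

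**Pre-screening.** Recruitment {15} has door-to-door staff "identify children that are in the age range of 6–59 months with a MUAC >125 mm but WAZ <−3". Eligibility criteria {10} has "b) MUAC ≥125 mm, (c) WAZ <−3". The section on the coordinating centre {5d} says the pre-screeners work from the eligibility criteria. Recruitment {15} also says that the referral card goes to a child whom the pre-screener has found eligible, with confirmation later at the research site.

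**The concern.** A subgroup factor needs levels that exclude one another and together cover the cohort. Mixing HAZ and WHZ in one factor breaks both conditions. It matters more here than in a general sample. Every child has WAZ <−3, so a child who is not wasted is usually light because he or she is short. A no-stunting group picked by WHZ would therefore tend to hold stunted children.

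The treatment rule adds to this. The standard arm gives or withholds RUTF according to WHZ. If the reference level of a stunting factor is really a WHZ level, simplified versus standard in that level is RUTF versus nothing, and any interaction would be labelled as stunting when its source is the allocation rule. Whether short, underweight children respond to treatment is part of the trial's rationale.

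The pre-screening wording raises a smaller question: whether eligible children reading exactly 125 mm were referred at all.

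**Working it through.** **1. Literal reading of subgroup analysis (3).** Cross HAZ bands with the stated WHZ condition:

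| HAZ at enrolment | WHZ >−2 | WHZ ≤−2 |
|---|---|---|
| <−3 | severe **and** no stunting | severe |
| ≥−3 and <−2 | moderate **and** no stunting | moderate |
| ≥−2 | no stunting | **no group** |

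Two cells carry two labels and one carries none. (The moderate level lacks an operator before −2, so exactly −2 is loosely assigned.) This step needs no assumption.

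**2. Treatment within the literal reference level.** All children in it have WHZ >−2. Simplified arm: one sachet a day. Standard arm: WHZ ≥−2, hence none. Control arm: none. So simplified versus standard is treated versus untreated in this level, whereas the two HAZ-defined levels mix treated and untreated standard-arm children. The simplified versus control comparison has no WHZ-dependent allocation; there the fault is only that the groups are wrong.

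**3. How far the literal group could depart from the intended one (illustration, not a document figure).** Assumed: independent normal HAZ (mean −1.2 or −1.5, SD 1.2) and WHZ (mean −0.7 or −0.9, SD 1.05); WAZ = a·HAZ + b·WHZ + noise (SD 0.1), with (a, b) = (0.6, 0.7), (0.65, 0.75) or (0.7, 0.8). Restricted to WAZ <−3; the MUAC ≥125 mm condition is not modelled. Over the six settings:

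- 36–49% have WHZ >−2.
- Of these, at least 99% have HAZ <−2, and 61–91% have HAZ <−3.
- 12–21% of the cohort have HAZ ≥−2; at most about 1% of those have WHZ >−2.

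Under this model the literal reference group is nearly the reverse of the intended one.

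**4. Share reading exactly 125 mm (illustration).** Assumed: MUAC recorded to 1 mm, as Anthropometry states for study visits; Recruitment gives no precision for pre-screening.

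- Normal MUAC, mean 128–135 mm, SD 5–9 mm: [Φ((125.5−m)/s) − Φ((124.5−m)/s)] / [1 − Φ((124.5−m)/s)] runs from 1.1% (m = 135, s = 5) to 8.8% (m = 128, s = 5).
- Exponential excess over 125 mm, mean 8–15 mm: 1 − exp(−1/8) = 12%; 1 − exp(−1/15) = 6%.

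Taken together, about 1–12%. The exponential form peaks at the cut-off and so favours a high share.

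**5. Sample size.** 146/0.70 = 208.6, giving 209; 475/0.80 = 593.75, giving 594; 209 + 594 + 594 = 1397, as stated. The inputs are the WAZ difference or margin, SD, power, error rate and missingness. Neither cut-off in dispute enters.

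**The case against.** The strongest reply is that both are drafting slips which the document itself resolves. The Background, subgroup analysis (1) and the other two levels of (3) all use HAZ, and Statistical methods {20a} speaks of HAZ categories. An analyst coding one three-level variable would find that some children fit two levels and would correct it. Height is measured at every visit, so nothing is lost. That is fair, and it rules out a stronger reading that a reader might infer: that the trial will report a wrong answer on whether stunted children respond. The article does not show that the literal rule will be coded, and an analysis plan that is not shown may state it correctly. What stands is that the one place giving cut-offs gives a wrong one.

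On pre-screening, a reader might infer that eligible children at 125 mm were turned away. The article does not establish this. Section {5d} says pre-screeners apply the eligibility criteria, and the Abstract, Objectives and Discussion all have ≥125 mm. It is equally not excluded: confirmation at the site cannot recover a child who was never given a card. Any loss would come before randomisation, so it would narrow the population slightly and leave the comparison between arms unbiased. Recruitment closed in October 2023, so new wording cannot alter who was enrolled.

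It is also fair that the sizes in the two illustrations rest on distributions the document does not give. A claim that the reference group is almost wholly misclassified, or a firm percentage at 125 mm, goes further than the text allows.

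**Conclusion.** The point holds for the subgroup definition. As written, the stunting factor is neither exclusive nor exhaustive; this follows from the text alone. Its reference level coincides with no wasting, and in simplified versus standard that level is, by the treatment rule, treated against untreated. How many children would be misplaced depends on the joint distribution of HAZ and WHZ, which the article does not give; the modelled figures show only that the number could be large.

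The scope is limited to the stunting subgroup and, by extension, the HAZ interaction. The primary outcome, both primary hypotheses and the sample size are unaffected.

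The pre-screening point is minor: three sections disagree or can be read differently, field practice is not visible, and the share at exactly 125 mm is unknown.

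**What to change.** In {20b}, before the intervention code is released:

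- No stunting: HAZ ≥−2. Moderate stunting: HAZ ≥−3 and <−2. Severe stunting: HAZ <−3.
- No wasting: WHZ ≥−2. Moderate wasting: WHZ ≥−3 and <−2. Severe wasting: WHZ <−3. This assigns the value −2, which the present wording leaves open, and matches the boundary in the treatment rule.
- State that the HAZ and WHZ categories in the {20a} interactions are these.

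When reporting the HAZ interaction for simplified versus standard, show the WHZ mix within each HAZ level. Because all children have WAZ <−3, HAZ and WHZ will tend to run in opposite directions, and the WHZ rule may still show through correctly defined stunting groups.

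Reconcile Recruitment {15}, Eligibility {10} and section {5d} on the MUAC cut-off, and state in the trial report which one the pre-screeners used. If it was >125 mm, say that children at 125 mm were not referred.

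Cost: a few corrected lines and one reporting sentence. No new data, no change for participants and no change to sample size. Follow-up was due to finish by the end of April 2024 with analysis after it; a correction dated before unblinding avoids any suggestion that the subgroups were chosen after seeing results.

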### Methods in analysis to handle protocol non-adherence and any statistical methods to handle missing data {20c}

All analyses will be carried out in an all available case basis, i.e., all study participants will be included in the analysis. In case of missing outcome data at the primary and secondary endpoints of 2 and 6 months respectively, imputation will be performed using key variables such as age, sex, time since enrolment, randomization arm, treatment status, other anthropometry, and any other (previous or later) outcome measure data points. The primary analysis will apply a “de facto” principle [51] answering to the question of whether the treatment works in a real-life setting, and will thus analyze the data irrespective of degree of adherence to their treatment group. In addition, a “de jure” analysis will be performed to estimate the efficacy of the treatment in a best-case scenario, adjusting for the actual dose obtained, simulating a per-protocol analysis, as per the recommendations for non-inferiority analysis [52, 53]

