### Outcomes {12}

Both primary and secondary outcomes will be reported for all 3 arms at both 2 (primary endpoint) and 6 months (secondary endpoint) post-enrolment. The primary outcome is the mean WAZ of children. WAZ has been shown to be strongly associated with mortality and thus acts as a proxy of the ultimate goal of reducing child mortality. Increase in WAZ can be both related to the increase in HAZ or WHZ, which is an added value as it enables appreciating and aggregating both outcomes that are positive. As a continuous measure, WAZ is well adapted to capture the response to treatment among the study population as it will more easily capture smaller benefits of treatment compared to categorical outcomes.

Secondary outcomes include (a) proportion of children with WAZ <−3, (b) mean MUAC of children, (c) mean WHZ and HAZ, (d) proportion of children with WHZ <−3 or HAZ <−3, (e) mean skinfold thickness measures and mean skinfold thickness per age percentile, (f) mean fat-free mass and fat mass, fat-free mass index and fat mass index, (g) mean hemoglobin measure, and (h) change in all these outcomes from enrolment to endpoint. In addition, the proportion of children exiting the study at any time point due to a MUAC <125 mm or edema or diseased or hospitalized will be reported across arms. Finally, treatment outcomes will be reported for the 2 treatment groups including the percent recovered, defaulted, non-response, transferred to inpatient care, and died. The study exit status will be reported for all 3 arms including completion of the 6-month follow-up, developed a MUAC <125mm or edema during the study, abandoned study, lost-to-follow-up, and died.

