### Sample size {14}

Based on previous work on a similar population and similar intervention [48] we assumed a similar response to treatment and a similar SD for WAZ. Thus, for looking at hypothesis 1, we set an objective of measuring a meaningful impact of the simplified treatment (compared to no treatment) at a difference of 0.4 *z*-scores in WAZ. For calculating the sample size, we applied (a) SD of 1.1 WAZ, (b) power of 80%, (c) probability of type 1 error of 2.5%, and (d) obtained a sample size of 146 per group. Accounting for not having measures for 30% of children (particularly in the control arm) at 2 months due to (a) defaulting, lost-to-follow-up, or death (10%) or (b) development of MUAC <125 mm or edema (20%), we estimated needing 209 children in both control and simplified treatment arms each.

For looking at hypothesis 2 we set an objective of measuring a meaningful non-inferiority margin of 0.2 *z*-scores in WAZ. For calculating the sample size, we applied (1) SD of 1.1 WAZ, (2) non-inferiority margin of 0.2, (3) power of 80%, and (4) probability of type 1 error of 2.5% and obtained a sample size of 475 per group. Accounting for not having measures for 20% of children at 2 months due to (a) defaulting, lost-to-follow-up, or death (10%) or (b) development of MUAC <125 mm or edema (10%), we need 594 children in simplified and standard treatment arms each.

To be able to explore both hypotheses, we need 209 children in the control arm and 594 children in both the simplified and standard treatment arms meaning a total of 1397 children.

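### The imputation rule makes no exception for death, so as written children who died receive a WAZ that does not exist, and some can be counted as WAZ ≥−3

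*Protocol article*

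**What the plan says.** Three places in the protocol article bear on this.

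- **Missing data {20c}.** The analysis set is everyone: "All analyses will be carried out in an all available case basis, i.e., all study participants will be included in the analysis". The rule that follows is general: "In case of missing outcome data at the primary and secondary endpoints of 2 and 6 months respectively, imputation will be performed". The predictors include "age, sex, time since enrolment, randomization arm, treatment status, other anthropometry, and any other (previous or later) outcome measure data points". No reason for missingness is set apart.
- **Sample size {14}.** Death is one of the reasons for having no 2-month value. For the non-inferiority comparison: "Accounting for not having measures for 20% of children at 2 months due to (a) defaulting, lost-to-follow-up, or death (10" (the last figure is a percentage). The superiority calculation allows for 30% missing and names the same 10% group.
- **Outcomes {12}.** The primary outcome is mean WAZ at 2 months, repeated at 6 months. Secondary outcome (a) is the proportion below −3, and outcome (d) uses WHZ <−3 or HAZ <−3. WAZ was chosen because it "acts as a proxy of the ultimate goal of reducing child mortality". Deaths are also to be listed by arm as a study exit status, and the statistical methods section {20a} repeats this as counts and percentages for all three groups.

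**The concern.** A child who missed the 2-month visit has a WAZ that nobody recorded. A child who died has none. Imputation suits the first case and has no meaning in the second, yet the rule treats both alike.

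The imputation model can learn only from children who were measured, so it returns values for a living child. For outcome (a) such a value can fall at or above −3, and the death then counts as a child who is no longer severely underweight. MUAC, hemoglobin, skinfolds and body composition have the same problem.

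The rule also fits poorly with two of the plan's own choices. The primary analysis follows a *de facto* principle, asking how treatment works in real life, whereas growth imputed beyond death answers a hypothetical question. And WAZ was chosen for its link with mortality. At stake is a clear definition of what mean WAZ and outcome (a) estimate, more than a large numerical error.

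**Working it through.** **1. Does the rule reach deaths?** Section {20c} says "all study participants will be included in the analysis" and imputes any missing 2- or 6-month outcome. Section {14} counts a death as a missing measure. No other section exempts deaths, assigns them a value, or limits WAZ to children alive. Together these statements cover children who died.

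**2. Can the listed predictors repair it?** Treatment status might carry the exit category for death. But no child who died before an endpoint has an observed value at that endpoint, so an effect of that category cannot be estimated. The control arm has no treatment exit criteria at all.

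**3. The plan's own figures.**
- Non-inferiority: 2 × (1.960 + 0.842)² × 1.1² / 0.2² = 475 per group, and 475 / 0.8 = 594.
- Superiority with two-sided 2.5%: 2 × (2.241 + 0.842)² × 1.1² / 0.4² = 144. The t-based version gives 145.03, rounded up to the stated 146, and 146 / 0.7 = 209.
- Total: 209 + 2 × 594 = 1397.

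The figures reproduce. They already set aside children without a measure, so this point does not touch the sample size.

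**4. Number of deaths (assumed).** The protocol gives only 10%, shared by default, loss to follow-up and death. If all of it were death, that would be 21 of 209 and 59 of 594. I assume 0.5% to 2% dead by the endpoint:
- control: 209 × 0.005 to 0.02 = 1 to 4
- each treated arm: 594 × 0.005 to 0.02 = 3 to 12

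**5. Outcome (a).** If imputed values are normal with mean m and SD s, the share at or above −3 is 1 − Φ((−3 − m)/s). I assume m from −3.5 to −2.8 and s from 0.5 to 1.1.

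| m | s = 0.5 | s = 1.1 |
|---|---|---|
| −3.5 | 0.159 | 0.325 |
| −3.2 | 0.345 | 0.428 |
| −3.0 | 0.500 | 0.500 |
| −2.8 | 0.655 | 0.572 |

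So 16% to 66% of imputed deaths would count as not severely underweight. Compared with counting death as unfavourable, the arm's proportion below −3 is too low by 0.005 × 0.159 = 0.08 points up to 0.02 × 0.655 = 1.3 points. In a treated arm, 594 × 0.0008 to 0.0131 is about 0.5 to 8 children.

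**6. Mean WAZ against a survivor mean.** Let p be the death share, S the survivor mean and I the mean imputed to the dead. Under the rule the arm mean is (1 − p)S + pI = S + p(I − S).
- If I = S, the difference is 0.
- If I is 0.5 z lower (illustrative), it is −0.5 × 0.005 to 0.02 = −0.0025 to −0.01 WAZ, or 1.25% to 5% of the 0.2 margin, and it counts against the arm with deaths.

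**7. Mean WAZ against a worst-value score.** This is a different comparator. If the imputed value lies 1 to 2.2 z above the score a death would otherwise get (2.2 is two SDs of 1.1), and the arms differ by 0.5 to 2 points in deaths, the contrast moves by 1 × 0.005 = 0.005 up to 2.2 × 0.02 = 0.044 WAZ. That is 2.5% to 22% of the margin. The top end needs 12 deaths in one treated arm and none in the other.

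**The case against.** **This belongs to the analysis plan.** Section {20c} never mentions death, gives no imputation model, and is a condensed account; where imputation stops is often settled in an SAP, which is not shown here. That would answer a missing rule. Here a rule is stated, and applied as written it includes deaths. A plan that handled them properly would have to narrow it.

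**The term available case implies no imputation.** Section {20c} itself explains the term as including everyone and then prescribes imputation.

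**The harm to mean WAZ is small.** This stands. A reader might infer that the rule tilts the non-inferiority comparison toward the arm with more deaths. Step 6 does not support that: a survivor mean does not penalise deaths either, and low values before death would make the current rule slightly harsher. The larger shift in step 7 is relative to worst-value scoring only.

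**Imputed values need not be favourable.** This stands in part. All children enter below −3 and are measured fortnightly, and earlier measurements feed the imputation, so a child who declined before death would tend to draw a low value. A reader might infer that about half of deaths would score as a success, or that the endpoint's meaning is reversed. The protocol supports neither; the share depends on assumptions and ranges widely.

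**Deaths are visible anyway.** Also true. Exit status by arm includes death, deaths are reported to the DSMB, and a composite of adverse exits is reported across arms (one of its terms may be meant as deceased). None of this changes how mean WAZ or outcome (a) is computed.

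**Conclusion.** The concern holds as a matter of definition. The stated rule imputes anthropometry, hemoglobin and body composition after death, and some of those children can be counted as WAZ ≥−3 on outcome (a).

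The effect on mean WAZ is probably small and close to nil compared with a survivor mean. For outcome (a) it is about 0.1 to 1.3 percentage points in an arm with 0.5% to 2% deaths. It matters more at 6 months, when more deaths have accrued. All sizes rest on assumed death rates and assumed imputed values, because the protocol gives neither.

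The protocol does not support a conclusion that the primary comparison is materially biased or that mortality would be concealed.

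**What to change.** 1. State in {20c} and in the SAP that imputation is limited to children not known to have died at the endpoint concerned, and describe mean WAZ, like the other continuous outcomes, as estimated among children alive.
2. Count death as unfavourable in the binary anthropometric outcomes: WAZ <−3, and WHZ <−3 or HAZ <−3.
3. Add one sensitivity analysis of the primary outcome with deaths given the worst rank, because a survivor mean alone does not penalise deaths. Show the planned deaths by arm beside the primary result.

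The study exit categories already separate children who died, those confirmed alive after leaving, and those whose vital status is unknown, so no new data are needed. Sample size and conduct do not change. Investigators are to stay blinded until data cleaning and initial analyses are complete, so the rule can be fixed before the allocation code is released.

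The cost is a few sentences and one extra analysis. There are two small downsides. The mean-WAZ estimate becomes conditional on survival. And a rank analysis gives no WAZ difference to set against the 0.2 margin, so for non-inferiority it supports the main result without replacing it.
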